## Abstract

**Background:**

Compared to other children, those with disability have additional challenges to being physically active. Prader-Willi Syndrome is a genetic form of childhood obesity that is characterized by hypotonia, growth hormone deficiency, behavioral, and cognitive disability. In children, the low prevalence of this syndrome (1 in 10,000 to 15,000 live births) makes group-based physical activity interventions difficult. In contrast, the home environment presents a natural venue to establish a physical activity routine for this population. This manuscript describes the design of a parent-led physical activity intervention incorporating playground and interactive console-based games to increase physical activity participation in youth with and without Prader-Willi Syndrome.

**Methods/Design:**

The study participants will be 115 youth ages 8-15 y (45 with the syndrome and 70 without the syndrome but categorized as obese). The study will use a parallel design with the control group receiving the intervention after serving as control. Participants will be expected to complete a physical activity curriculum 4 days a week for 6 months including playground games 2 days a week and interactive console games 2 days a week. Parents will be trained at baseline and then provided with a curriculum and equipment to guide their implementation of the program. Tips related to scheduling and coping with barriers to daily program implementation will be provided. Throughout, parents will be contacted by phone once a week (weeks 1-4) and then every other week to receive support in between visits. Measurements of children and parents will be obtained at baseline, 12 weeks, and at the end (week 24) of the intervention. Children main outcomes include physical activity (accelerometry), body composition (dual x-ray absorptiometry), motor proficiency (Bruininks-Oseretsky Test of Motor Proficiency), quality of life and physical activity self-efficacy (questionnaires). Intervention compliance will be monitored using mail-in daily self-report checklists.

**Discussion:**

This parent-guided physical activity intervention aims to increase physical activity by using a curriculum that builds physical activity related self-confidence through the development and/or enhancement of motor skill competency. Ultimately, helping children develop these skills as well as joy in being physically active will translate into sustained behavior change.

**Trial registration:**

Current Controlled Trial: NCT02058342

## Background

The U.S. Department of Health and Human Services, the Subcommittee of the President’s Council on Fitness, Sports & Nutrition and the American College of Sports Medicine, among others, recommend that children and youth participate in 60 minutes a day of moderate to vigorous physical activity (PA) [1,2]. It is further recommended that the content of the PA include aerobic, muscle, and bone-strengthening activities [2]. Similar recommendations have been put forward to stimulate the participation of children with disability in sports and recreational activities as well as to achieve the same expected 60 minutes-a-day of moderate-to-vigorous PA (MVPA) [3]. Recommendations reside on the fact that PA provides numerous health benefits for children such as helping regulate blood sugar, insulin, lipids and blood pressure, maintaining a healthy weight, developing stronger bones, building muscle mass and improving physical fitness [2,4,5]. Additionally PA is associated with increased self-efficacy, less depression and anxiety and ultimately a higher quality of life [2].

Currently, 58% of children ages 6-11 y are not meeting these recommended guidelines [6]. And, available studies in children and adolescents with physical and/or cognitive disability suggest that their participation in PA may be lower [7-11] and does not meet the recommended minutes [11]. Low participation in PA has been linked to the increasing prevalence of obesity in youth with disability [7].

Prader-Willi Syndrome (PWS) is a rare congenital disease stemming from an alteration or the lack of expression of the paternal chromosome 15 in the locus 13-15q. This syndrome is the best-characterized form of childhood obesity and people with PWS have abnormally high body fat percentage and low lean mass [12]. In addition, having PWS is associated with innate lethargy, delayed motor development, lower motor competencies, lower cognitive function, and behavioral challenges, with most individuals presenting with physical and intellectual disability [13]. Children and adults with this condition exhibit low levels of ambulatory PA [14,15], little vigorous PA, and appear to perform few activities aimed at improving muscular strength [16]. In children with PWS, more PA has been associated with lower body mass index (BMI), and reduced engagement in self-injury behavior common to PWS such as skin picking [17]. To date, four approaches to promoting PA in persons with PWS have been evaluated: two strength-training routines delivered at home for children [18,19], and a walking and an at home strengthening programs for adults [20,21]. Although these programs were successful at improving body composition, spontaneous physical activity and general fitness levels, none of these approaches considered the multiple dimensions of physical fitness (e.g., aerobic endurance, strength, flexibility), the development and improvement of motor competencies, or the concept of developing a fun family PA routine.

### Theoretical framework

Social Cognitive Theory was the theoretical framework used to guide the development and implementation of this physical activity intervention [22]. Self-efficacy is a focal determinant of Social Cognitive Theory and has often been a key target of PA interventions [23]. For individuals to adopt and maintain a healthy lifestyle including behaviors such as PA, the person needs to have the self-regulatory skills and the confidence to regulate the behavior [24]. Self-regulatory skills (i.e. self-monitoring, planning, coping with barriers) have been related to improving PA behavior by increasing adherence in adults [25] and often are included in interventions that employ a social cognitive theory framework [26].

Individuals may manage or regulate their own behavior and/or have another individual serve as a proxy to manage their behavior [27]. In children, parents may serve as a proxy and aid in the management and regulation of their child’s PA by scheduling opportunities for PA and providing equipment and/or transportation. Further, it might be speculated that in children with disability the parent may take a more active role in regulating the child’s behavior. The primary assumption of Social Cognitive Theory is that behavior, environment, and the person are reciprocally linked [28]. A key part of children’s environment involves the influence from parents as they play an essential role in the development of their children’s behaviors, attitudes, and values. In fact, previous studies have shown that parental influences are associated with children being more physically active [29]. Parents have the potential not only to serve as proxy agents for their children’s PA but also to directly influence their children’s perceptions and behaviors. By targeting aspects of the person (e.g., PA self-efficacy) and the environment (e.g., social influences received from parents), an associated change in the child’s physical activity may emerge.

### Successful approaches to increase PA in children

In children without disability, only a small number of interventions have been designed to improve motor skills [30,31] since children who are more proficient in different motor domains (e.g., agility, balance, coordination, bilateral coordination, muscle strength, and aerobic endurance) are likely to be more physically active [32-34]. Activity cards or manuals containing progressive games and exercises have been successfully used in school settings and after school programs to increase MVPA and improve cardiovascular fitness [35,36]. Most recently, interactive console-based games have been used to increase PA [37,38] and even promote weight loss [39]. In those with disability, the use of interactive console-based games seems a promising area of study as positive results in gross motor function have been shown for programs in children with cerebral palsy [40,41] as well as Down syndrome [42].

Studies targeting lifestyle changes in children with obesity, inclusion of the family has been identified as a key component in effective interventions [43]. In fact, in children with disability, family participation in PA has been shown to be a positive predictor of the child’s PA [9]. Unfortunately, only a few studies have explored the feasibility of family interventions [44-46]; some interventions have targeted solely the parents as agents of change [47-49] and other interventions have included parent-child dyads participating in home-based PA programs [50,51]. Co-activity, in which parents and children participate in physical activity together, is positively associated with PA in children [52], and thus appears to be important to target in a PA intervention. A recent report on strategies to promote PA in youth highlighted the need to test strategies that can take place at home and involve the parents or family [2].

### The development of the active play @ home curriculum

Considering the abilities, needs, constraints, and preferences of children with PWS and their parents as well as previous intervention approaches that proved successful in this population [18,19] we developed a home-based PA curriculum called Active Play @ Home. This well-rounded and varied PA curriculum includes all the essential exercise components recommended in the national guidelines (progressive games and exercises targeting cardiovascular fitness, muscular strength and endurance) while also targeting motor skill competencies. In addition, the curriculum incorporates the use of interactive console-based games that were carefully chosen to stimulate fitness components as well as specific motor skill competencies. The curriculum therefore blends more traditional playground games and exercises with interactive console-based games. The inclusion of the interactive console-based games aims to provide the children with a choice of activities that can be performed indoors while the playground games can be played outdoors. The curriculum is designed to involve an adult leader and one child; however, all activities can be played with more than one child in the home environment.

The goal of the Active Play @ Home study is to determine if a parent-led PA curriculum incorporating playground games and interactive console-based games can increase levels of PA and lead to positive motor and health-related outcomes in children with PWS and in children without the syndrome but who are obese. Changes in PA and motor and health-related parameters will be evaluated in these two groups in comparison to control groups following a 24-week PA intervention. The primary hypothesis is that an age-appropriate home-based PA intervention will increase PA levels in children with and without PWS. The secondary hypotheses include the following: 1) motor proficiency, central sensory reception and integration, and body composition will significantly improve in children, with and without PWS, following completion of the home-based PA intervention, and 2) self-efficacy and quality of life will increase significantly in children, with and without PWS, who complete the home-based PA intervention.

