## Methods/Design

### Study design

The Active Play @ Home study will evaluate the effectiveness of a 24-week PA intervention on select motor and health–related parameters in children with PWS and children with obesity but without PWS. The study has a quasi-experimental design with semi-random assignment to an intervention group or a wait-listed control group. The intervention group will consist of families with a child with PWS (n=35) and families with a child who is obese (n=50). Ten additional families with a child with PWS will be assigned to a wait-list control group and 20 families with an obese child without PWS will also serve as a wait-list group. Both wait-listed groups will serve as control groups prior to being enrolled in the PA intervention. Groups of two to four families will complete all baseline and follow-up testing on the same day throughout the study. The semi-random assignment consists of a priori established participant cohorts for both intervention and control groups. Upon recruitment, participants will be provided with tentative dates for their visits and their randomization to the cohort (intervention vs. control) will be based on their date preferences. Ethic committee approvals have been obtained from the California State University Fullerton Institutional Review Board and the United States Army Human Research Protection Office. During the first visit, after all study procedures are verbally explained, participants will have time to read the informed assent and consent forms and ask questions regarding the procedures. Afterwards, children participants will sign the informed assent form and their parents or guardians will sign the informed consent form. Figure 1 presents a timeline of the study procedures.

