### Data analyses

The main purpose of this study is to investigate short-term changes (immediately following the 24-week intervention) in PA, motor proficiency, and health-related outcomes in children with and without disability following completion of a physical activity program conducted in the home environment. A 2 (time: pre, post) by 2 (group: control, intervention) by 2 (youth: obese or PWS) mixed model ANOVA will be used to assess changes in the primary outcome (i.e., physical activity). Similar analyses will also be performed to assess changes in gross motor proficiency, body composition, and central sensory reception and integration. Other changes that will also be evaluated using mixed model ANOVAs include changes in quality of life, child self-efficacy, parent regulatory efficacy, and parent social influences. Potential confounders will serve as covariates where appropriate.

A power analysis was performed using G*Power 3.1.9 to identify the appropriate sample size for a power of .95, an alpha level of .05 and a correlation between time points was assumed to be .50. A small to moderate effect size (*f*=.20) was chosen, given the variability in physical activity expected in children with PWS [15]. A sample size of 84 was identified to provide sufficient power to detect an interaction. Given a 30% probability of drop-outs, 115 children will be recruited.

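### The primary hypothesis concerns each of two populations, but the stated power of .95 applies only to a pooled, equally split interaction; at the planning effect, power for PWS is about .59, or .44 after drop-out

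*Protocol article*

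**What the plan says.** The hypothesis, in the section on the development of the curriculum, covers both populations: "The primary hypothesis is that an age-appropriate home-based PA intervention will increase PA levels in children with and without PWS". The same paragraph describes the comparison: "Changes in PA and motor and health-related parameters will be evaluated in these two groups in comparison to control groups".

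Study design puts 35 children with PWS and 50 obese children in the intervention group. On the PWS controls it says: "Ten additional families with a child with PWS will be assigned to a wait-list control group". The obese controls number 20.

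Data analyses plans a time by group by youth (2x2x2) mixed ANOVA for physical activity, where youth means obese or PWS. The sample size was found "for a power of .95, an alpha level of .05 and a correlation between time points was assumed to be .50". On the effect, "A small to moderate effect size (*f*=.20) was chosen". The result is: "A sample size of 84 was identified to provide sufficient power to detect an interaction". Recruitment of 115 allows for 30% drop-out. The section does not say which interaction is meant, and it gives no power for either population on its own.

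**The concern.** A hypothesis about children with and without PWS, each set against controls, needs two answers. The sample-size statement supplies the power for one.

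Of the interactions in the planned model, the time-by-group term averages the effect over both populations, so obese children alone can make it significant. The three-way term asks whether the two effects differ, not whether there is an effect in PWS. With ten PWS controls it is also a weak test of that difference.

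At stake is what the trial may conclude about PWS. The PWS comparison is the smallest and most unevenly split part of the design, and a reader of the article has no figure for how much it can show.

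**Working it through.** **Inputs.** Power .95, alpha .05, r=.50, f=.20, N=84, drop-out 30% (Data analyses). PWS 35 vs 10 and obese 50 vs 20 (Study design).

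**1. Reproduce N=84.** For a repeated-measures within-between interaction with m=2 times and k groups, the noncentrality is f²·N·m/(1−r), with (k−1)(m−1) and (N−k)(m−1) degrees of freedom.
- k=2, N=84: noncentrality = .04×84×2/.5 = 13.44, power .952. N=84 is the smallest N reaching .95.
- k=4 (the four group-by-youth cells): N=112 is needed.

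So 84 is correct arithmetic for intervention vs control, 42 per group, without the youth factor.

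**2. Express f=.20 on the change score.** √13.44 = 3.666. A two-sample t test on change with 42 vs 42 has noncentrality d·√(42×42/84) = 4.583d. Equating the two gives d = .80. With r=.50 the SD of change is SD·√(2(1−.50)) = SD, so the planning effect is a .8 SD difference in change. The t test with 42 vs 42 also gives power .952.

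**3. Power within each population.** Noncentrality = .8·√(n1·n2/(n1+n2)), two-sided .05, noncentral t.

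| Comparison | n | Noncentrality | Power |
|---|---|---|---|
| PWS, no loss | 35 vs 10 | 2.23 | .59 |
| PWS, 30% loss | 24.5 vs 7 | 1.87 | .44 |
| Obese, no loss | 50 vs 20 | 3.02 | .85 |
| Obese, 30% loss | 35 vs 14 | 2.53 | .70 |

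Using the error degrees of freedom of the whole model changes little. For PWS it gives .60 with no loss and .45 after loss (24 vs 7, 76 df).

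**4. Pooled interaction with the actual allocation, effect .8 SD in both populations.**
- No loss: .96 ignoring youth (85 vs 30); .95 as the unweighted average over the two populations.
- After 30% loss: .88 ignoring youth (59.5 vs 21); .84 unweighted.

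The fall after loss has two causes: the unequal split, and 115×.70 = 80.5 completers, which is fewer than 84.

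**5. Effect .8 SD in obese children, zero in PWS.**
- Three-way term, no loss: SE = √(1/35+1/10+1/50+1/20) = .446; .8/.446 = 1.80; power .43.
- Three-way term, after loss (24, 7, 35, 14): SE = √(1/24+1/7+1/35+1/14) = .533; .8/.533 = 1.50; power .32.
- Pooled time-by-group term: still significant in 43% (unweighted) to 67% (weighted by information) of trials with no loss, and in 32% to 52% after loss.

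**6. Precision in PWS after loss.** The 95% half-width is t(.975; 29.5)·√(1/24.5+1/7) = 2.04×.429 = .88 SD, wider than the .8 SD planning effect. For power .80 with 24 vs 7, the true effect would have to be about 1.25 SD.

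**The case against.** The strongest reply is that the article makes no false power claim. A reader might infer that .95 was promised for PWS, but the document attaches it only to an unspecified interaction. With no loss, the pooled interaction does reach about .95. A reader might also infer that a non-significant three-way term is to be taken as benefit in both populations. No interpretation rule of that kind is written, and the text says that both groups will be compared with controls. Both objections stand.

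The youth factor is in the planned model, so within-population contrasts can be taken from it, and an article may leave that detail to a fuller plan. This is also right, but it does not remove the mismatch between the hypothesis, the allocation and the power statement, all of which the article gives. Extracting the PWS contrast leaves its power at about .45 after loss.

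A third stronger reading is that the model must allow different residual variances. The article mentions variability of activity in PWS only when justifying its effect size. It does not say that the variance differs from that of obese children. Separate variances are a modelling preference and are not part of this point.

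Finally, PWS is rare, so a small PWS group was foreseeable, and .44 is one drop-out scenario. Both are fair. Rarity explains the number of children, not the absence of a power figure for them, and with no loss at all the figure is still only .59.

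**Conclusion.** The point holds as a mismatch between what is hypothesised and what is powered. At the plan's own effect size, power is about .59 for PWS and .85 for obese children with no loss, and about .44 and .70 after 30% loss. The pooled interaction itself falls to about .84 to .88 after that loss. Neither it nor the three-way term tests the effect in PWS.

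The figures assume that f=.20 holds within each population, that r=.50, and that loss is equal across arms. If f=.20 is kept and r is varied from .3 to .7 (an assumed range, not in the document), PWS power after loss runs from .33 to .64.

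If the sponsor meant the hypothesis as one pooled statement, the low PWS power would be a limitation rather than a contradiction. The wording about two groups, each compared with controls, favours the separate reading. The matter concerns the primary hypothesis and should be corrected, but it does not invalidate the design.

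**What to change.** - Name the group difference in change within PWS and the group difference in change within obese children, both from the planned 2x2x2 model, as the tests of the primary hypothesis. Report each with a 95% confidence interval, and state the expected precision (half-width about .88 SD for PWS after loss).
- State that neither the pooled time-by-group term nor a non-significant three-way term, taken alone, supports a claim of benefit in PWS.
- Say that N=84 refers to the pooled two-group interaction with equal allocation, and restate power per population with and without drop-out: .59 and .44 for PWS, .85 and .70 for obese children.

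The cost is analysis and power wording only; recruitment, allocation and intervention stay as they are. The change does not raise power in PWS, and the stated power becomes less favourable.

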## Methods/Design

### Study design

The Active Play @ Home study will evaluate the effectiveness of a 24-week PA intervention on select motor and health–related parameters in children with PWS and children with obesity but without PWS. The study has a quasi-experimental design with semi-random assignment to an intervention group or a wait-listed control group. The intervention group will consist of families with a child with PWS (n=35) and families with a child who is obese (n=50). Ten additional families with a child with PWS will be assigned to a wait-list control group and 20 families with an obese child without PWS will also serve as a wait-list group. Both wait-listed groups will serve as control groups prior to being enrolled in the PA intervention. Groups of two to four families will complete all baseline and follow-up testing on the same day throughout the study. The semi-random assignment consists of a priori established participant cohorts for both intervention and control groups. Upon recruitment, participants will be provided with tentative dates for their visits and their randomization to the cohort (intervention vs. control) will be based on their date preferences. Ethic committee approvals have been obtained from the California State University Fullerton Institutional Review Board and the United States Army Human Research Protection Office. During the first visit, after all study procedures are verbally explained, participants will have time to read the informed assent and consent forms and ask questions regarding the procedures. Afterwards, children participants will sign the informed assent form and their parents or guardians will sign the informed consent form. Figure 1 presents a timeline of the study procedures.

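### Arm is tied to cohorts chosen by visit date and families are tested in groups of two to four, but the planned ANOVA and the N of 84 treat children as independent; if change is positively correlated within groups, the group-by-time standard error is understated

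*Protocol article*

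**What the plan says.** Three statements in the Study design section bear on the unit of assignment.

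- Assignment: "The semi-random assignment consists of a priori established participant cohorts for both intervention and control groups". A family enters one by choosing dates: "their randomization to the cohort (intervention vs. control) will be based on their date preferences".
- Testing: "Groups of two to four families will complete all baseline and follow-up testing on the same day throughout the study".
- Size: the intervention arm has 35 families with a PWS child and 50 with an obese child, 85 in all. The wait-list arm has 10 and 20, 30 in all.

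The Data analyses section gives the primary model: "A 2 (time: pre, post) by 2 (group: control, intervention) by 2 (youth: obese or PWS) mixed model ANOVA will be used". It names no cohort, test-date or calendar term and adds only that potential confounders will be covariates where appropriate. The sample size of 84 is for power .95, alpha .05, f = .20 and a correlation of .50 between time points, with 115 recruited to allow for 30% dropout.

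The Physical activity section has the accelerometer worn for eight days from Sunday to Sunday and says that families attend data collection on Saturdays.

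**The concern.** The arm label belongs to a cohort before any family joins it. Visit dates determine the cohort, and a test-day group shares its visit dates throughout, so each group should lie within one arm. Families seen on the same Saturday would be expected to wear the monitor in the same week before and after the intervention. That is an inference, since the article does not date the wear week. They would then share weather, daylight and school term at both time points, and such shared influences enter the change score directly. Motor testing, balance testing and DXA may also share test-day effects.

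The comparison of change between arms is then a comparison between groups of families, while the error term is built from individual children. With positive within-group correlation, the group-by-time test rejects too often and its confidence interval is too narrow. The control arm contributes the fewest groups, so the degrees of freedom are also overstated.

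**Working it through.** **Inputs.** From the article: groups of 2 to 4 families, 85 and 30 families per arm, f = .20, correlation .50, alpha .05, power .95, 30% dropout. Assumed, because the article gives no value: ICC of the pre-post change of 0, .05, .10 and .20; mean group size 3; test-day groups nested within arm.

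**1. The plan's own figure.** For a two-group, two-time interaction, the noncentrality is λ = N·f²·m/(1−ρ), with m = 2 time points and N−2 error degrees of freedom. At N = 84, λ = 84 × .04 × 2/.50 = 13.44 and power is .952. The figure of 84 is reproduced. It contains no design effect, so it corresponds to an ICC of 0.

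**2. Design effect.** DE = 1 + (n−1)·ICC, where n is the group size. The true standard error is √DE times the reported one. The approximate type I error of the naive test is 2·[1 − Φ(1.96/√DE)]. Power at N = 84 and the required N come from dividing λ by DE, with equal arms as in the plan's calculation. For n = 3:

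| ICC (assumed) | DE | √DE | Type I error | Power at N = 84 | Evaluable N for power .95 |
|---|---|---|---|---|---|
| 0 | 1.00 | 1.00 | .050 | .952 | 84 |
| .05 | 1.10 | 1.05 | .062 | .932 | 92 |
| .10 | 1.20 | 1.10 | .074 | .911 | 100 |
| .20 | 1.40 | 1.18 | .098 | .865 | 116 |

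Over group sizes 2 to 4, the type I error runs from .056 to .068 at ICC .05, from .062 to .086 at ICC .10, and from .074 to .121 at ICC .20. Evaluable N runs from 88 to 96, 92 to 108, and 100 to 132.

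**3. Simulation under the null.** With 28 intervention and 10 control groups of three and an ordinary t-test on change (20,000 runs), rejection rates are about .062 / .073 / .10 at ICC .05 / .10 / .20. This agrees with the table.

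**4. Dropout.** With 30% loss, a group of three keeps on average 3 × .70 = 2.1 children, so there is less clustering left to ignore. Random loss in the same simulation gives about .057 / .065 / .085.

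**5. Number of groups.** If all 30 control families are tested in groups of 4 down to 2, there are 30/4 = 7.5 to 30/2 = 15 control groups, that is about 8 to 15. The article does not state this count.

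**The case against.** - **The unit is not stated.** The article mentions test-day groups and assignment cohorts in separate sentences and never equates them. One could even read cohort as the arm itself. This stands. The group sizes and the count of 8 to 15 control groups are therefore assumptions. If the cohorts are larger, the design effect at a given ICC is larger.
- **The direction is conditional.** A reader might infer that the standard errors are simply too small and that the test must err towards false positives. The documents do not support that: no ICC is given, and at ICC 0 nothing changes.
- **Sources of correlation are limited.** Parents deliver the programme at home, one family at a time, support is by telephone, and the primary outcome is worn individually over eight days. A shared training session is possible but not stated. This limits the likely ICC. It does not remove the shared calendar week, which acts on change.
- **The model may be elaborated elsewhere.** A condensed article can leave the random-effect structure to a fuller plan, and season could enter as a covariate. But the design and the model are both stated here and do not match. Fixed covariates for confounding are not a cohort error term.
- **Independent assignment of 115 children is not claimed.** Correct. The article states that "The study has a quasi-experimental design with semi-random assignment to an intervention group or a wait-listed control group". The figure calculated under independence is 84; 115 is the recruitment target.
- **A permutation test over cohorts would be one remedy.** It has no design basis here, because families chose their dates and cohort labels were not randomised.

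**Conclusion.** The point holds in conditional form. The stated model omits the unit that most likely carries the arm, and the N of 84 assumes an ICC of 0. If change is positively correlated within test-date groups, the group-by-time standard error is understated, by a modest amount at these group sizes. For groups of about three, type I error is about .06 to .10 over ICC .05 to .20, or about .057 to .085 after 30% dropout. At ICC 0 there is no effect.

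These figures rest on the assumed ICC range, on test-day groups lying within one arm, and on two to four families per group. The article supports the second only indirectly and does not equate groups with cohorts.

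A reader might also take this as the main weakness of the allocation, or think that a corrected standard error makes the comparison sound. Neither follows. Assignment by date preference leaves selection and calendar-time confounding that no error term removes.

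**What to change.** 1. State whether an assignment cohort and a test-day group are the same unit, and keep the cohort or test-date identifier in the analysis data.
2. Add a random cohort-by-time effect to the group-by-time analysis, with Satterthwaite or Kenward-Roger degrees of freedom. Cluster-robust standard errors with a small-sample correction are an alternative.
3. Note beside the sample size that 84 assumes an ICC of 0, and show the evaluable N over a stated ICC range.
4. Do not use a permutation test over cohorts.
5. Report the selection and calendar-time confounding from date-preference assignment as a separate limitation.

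The cost is one model term on information that the visit schedule already holds, and slightly wider intervals. With about two completers per group and few control groups, the cohort-by-time variance may be estimated at zero. The result then falls back to the planned analysis, and this should be reported.
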